## Abstract

**Background:**

The European school-based drug addiction prevention program Unplugged was adapted to the Brazilian context by the Ministry of Health and renamed #Tamojunto. Its first implementations, in the form of a public policy in Brazil, showed contradictory and different effects from those observed in Europe. Adaptations were made to #Tamojunto in 2018 to reintroduce the essential content of the original program.

**Methods:**

A parallel, two-arm, randomized controlled trial (RCT) will be conducted to evaluate the effectiveness of the new version of the school-based government program #Tamojunto2.0 for the prevention of drug use among 8th grade middle school students from 70 public schools in three Brazilian cities, totaling approximately 6.300 participating students distributed in 210 classes. For intervention, the experimental group will receive the 12 lessons of the #Tamojunto2.0 program under the supervision of a Brazilian Ministry of Health team. The control group will not receive any intervention. Information will be collected from the students at three time points: preintervention and 9 and 18 months postintervention. Multilevel analyses will be performed using the Gllamm Stata program to assess simultaneous differences in prevalence, in time and among groups for the outcomes of interest. Structural equation modeling will be used to evaluate the effectiveness of the intervention in changing the behavioral patterns of the adolescents through latent transition analysis. The effect of the mediators involved in the program effectiveness outcomes will also be analyzed. The program doses applied in all classes of the intervention group will be collected using a form completed by the teacher at the end of each lesson, indicating the activities taught and not taught in each lesson.

**Discussion:**

This study will show whether the #Tamojunto2.0 program can be expanded as a public policy for all schools with the aim of preventing drug use among Brazilian students.

**Trial registration:**

Brazilian Clinical Trials Registry (RBR-8cnkwq) under the name “Avaliação do Efeito do Programa de Prevenção Escolar ao Uso de Drogas #Tamojunto2.0, Versão 2018”, on August 30th, 2018 (http://www.ensaiosclinicos.gov.br/rg/RBR-8cnkwq/).

## Background

The abuse of alcohol and other drugs is currently a major public health issue [1], and adolescent substance use is considered one of the main risk behaviors for the development of subsequent problems, such as dependence [2], cognitive impairment [3] and psychiatric disorders [4]. In Brazil, 55.5% of students between the ages of 13 and 15 have reported the consumption of alcoholic beverages, and 9% have reported illicit drug use [5].

The high prevalence of drug use in adolescence and the early age of onset of this behavior show the need for prevention programs in these age groups [6, 7]. School-based prevention programs have been implemented worldwide to reduce or delay the onset of alcohol and other drug use among adolescents [8]. Among the prevention models that have been shown to be effective are those that consider the social influences on the initiation of consumption, working towards reducing the risk factors and increasing the protective factors [9–11].

In 2013, the Brazilian Ministry of Health (BMH), in partnership with the United Nations Office on Drugs and Crime (UNODC), carried out a cross-cultural adaptation of Unplugged—a school-based program for substance use prevention*,* which was called #Tamojunto in Brazil [12]. The program is based on the “Comprehensive Social Influence Model” [13], whose approach attempts to build specific skills in adolescents that enable them to manage social influences, deconstructing normative beliefs, and is based on reflections on the contexts of drug use and knowledge about drugs and their health effects. When evaluated in European countries, Unplugged produced significant reductions in reports of episodes of drunkenness, frequent use of marijuana [14], tobacco use and use of any drug [15].

After translation into Brazilian Portuguese and cultural adaptation, in 2014 and 2015, the first Brazilian study on the effectiveness of #Tamojunto was conducted through a randomized controlled trial in six cities involving a sample of 6391 students from 72 public schools. The short-term (nine month follow-up) [16] and long-term (21 month follow-up) results showed a negative effect on alcohol initiation [17]. The adolescents in the intervention group had a 30% higher risk (95%CI 1.13–1.49) at 9 months and a 13% higher risk (95%CI 1.01–1.27) [16] at 21 months for first alcohol use compared to those in the control group [17]. The main hypothesis to explain these iatrogenic results suggests inadequate cultural adaptations for the alcohol components. The adaptation did not include the original components that reinforced the nonuse of alcohol and emphasized only the prevention components aimed at avoiding alcohol intoxication, with an emphasis on harm reduction [18].

Considering the negative results of #Tamojunto, in 2018, there was a significant change in the activities and content of the lessons that addressed alcohol and its effects. This new adaptation of the material aims to reintroduce the central elements of the European Unplugged program [14] and now requires a new evaluation of its results in the Brazilian population before expanding it into a formal public policy. This new adaptation also comes with a change in its visual identity, and the name has been changed to #Tamojunto2.0.

It is important to emphasize that drug prevention programs based on a theoretical psychosocial framework usually have protective effects on other risk behaviors of adolescents [11], as they act on risk and protective factors shared by several negative health outcomes, such as violence and psychiatric disorders [19–21]. In this sense, it is also important to investigate the effects of the #Tamojunto2.0 program on secondary outcomes, such as violence and different psychiatric symptoms, in Brazil.

## Methods

### Aims

The main objective of the study is to evaluate the effectiveness of the school-based program #Tamojunto2.0 at 9 and 18 months of follow-up in the prevention of drug use (alcohol, tobacco, inhalants, marijuana, cocaine, crack and amphetamines) and binge drinking among Brazilian students. Our main hypothesis is that the #Tamojunto2.0 program will delay the first use of these drugs and will decrease the prevalence of use among students who participate in the intervention compared to the students in the control group.

The second objective of this study is to evaluate the effectiveness of the program at 9 and 18 months of follow-up in the prevention of school violence and psychiatric symptoms (depression, anxiety, *attention-deficit/hyperactivity disorder* and eating disorders) among Brazilian students. Our second hypothesis is that the #Tamojunto2.0 program will reduce the prevalence and incidence of secondary outcomes among students participating in the intervention compared to the students in the control group.

The third objective of the study is to evaluate the mediating effect of the skills taught by the program (decision-making skills, refusal skills, knowledge about drugs and beliefs about drugs) in reducing primary outcomes (alcohol, tobacco, marijuana, inhalant, cocaine, crack and amphetamine use and binge drinking) and secondary outcomes (reports of school violence and psychiatric symptoms), comparing the control and intervention groups at three different time points (0, 9 and 18 months). Our third hypothesis is that the improvement in the skills taught by the program will mediate the program’s effect on reducing the primary and secondary outcomes, as described by a logical model.

Finally, the fourth objective of the present study is to evaluate the program implementation fidelity to identify possible changes in the original content and to measure if the dose of the program offered to the students influences the effects of the program. Our fourth hypothesis is that the greater the dose of the program offered to the students and the smaller the changes to the original content are, the greater the effect of the program in the prevention of the proposed outcomes will be.

### Study design

A randomized controlled trial with two parallel groups (intervention and control) will be conducted to evaluate the effectiveness of the program for adolescents enrolled in 8th grade middle school in 70 public schools in three Brazilian cities, totaling approximately 6300 students distributed in 210 groups. Randomization will be conducted at the school level. Schools randomly selected to be part of the intervention group will offer the 12 lesson #Tamojunto2.0 program in the year 2019. Schools in the control group will not offer prevention programs or activities in 2019. The selection of schools and the allocation to the control or intervention group will be performed by a simple random draw from the list of the National Institute for Educational Studies and Research ‘Anísio Teixeira’ (INEP), which includes all schools from each municipality.

The baseline data (T1) will be collected two weeks before implementation of the program in February/March 2019, and the follow-up data will be collected at 9 months (T2) in November/December 2019 and at 18 months (T3), August/September 2020 after the initial data collection in August 2020. The data will be collected simultaneously for both groups. This protocol was prepared in accordance with SPIRIT 2013 [22], and the study will be conducted according to the CONSORT guidelines [23].

At the end of each lesson, all teachers in the experimental classes will complete a fidelity and dose form, stating which of the planned activities were or were not taught in the lesson and if the teacher made any changes. Figure 1 shows the study design flowchart.

**Fig. 1 Fig1:**
[figure not shown]
Flowchart of the general design of the effectiveness evaluation of Tamojunto 2.0

### Participants

Eighth-grade middle school students aged 12 to 14 years, enrolled in public schools from three Brazilian cities (Fortaleza, Eusébio - northeastern region - and São Paulo - southeastern region) will participate in the effectiveness evaluation of the program. The participating cities were recommended by the BMH, based on the identification of the municipalities in which there was already collaboration and a partnership with the local government for the application of the #Tamojunto2.0 program*.* In addition, the selected cities have large sociodemographic differences; the two cities in the northeast are poorer and less populous than São Paulo, which is the fifth most populous city and the tenth richest city in the world.

### Sample size calculation

The PASS 15.0 software was used to calculate the sample sizes of the two intervention groups in a cluster randomized design [24]. A sample size of at least 3150 adolescents in the control group and 3150 in the intervention group, distributed among 35 clusters (schools) with at least 90 subjects in each arm, will reach a power of 82% in identifying a difference between groups of 2.5% for the outcome of binge drinking in the past month, with an initial prevalence of 10%, a significance level of 5%, and an intraclass correlation of 0.005. Thus, it is necessary to ensure the inclusion of at least three 8th grade classes from each sampled school, with 35 schools in the intervention group and 35 in the control group. Therefore, 70 schools will be selected to ensure a minimum sample size of 6300 adolescents, considering possible losses to follow-up.

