### Data analysis of the randomized controlled trial

The data will initially be analyzed by a descriptive analysis, that is, qualitative variables will be summarized as numbers and percentages and numerical variables as means, standard deviations, medians, minima and maxima. Descriptive analyses will be performed for different patterns of drug use. This dataset will be used to calculate sample weights through the svy command in Stata so that the baseline data analysis can be presented in an expanded form, aiming at correcting for losses and extrapolating the data to the sample universe [39, 40].

All analyses will be carried out in the two samples: “intention to treat” (ITT), which will include all the participating classes that received at least one lesson of the program, and “per protocol” (PP). The PP analysis will include only those classes that receive the complete protocol (12 lessons), determined based on evaluating the dose and fidelity form that will be completed by the teacher at the end of each lesson.

Because the data are collected in groups, they are not independent at two levels (school and class), and the measures of association should be analyzed through GLLAMM (Generalized Linear Latent and Mixed Models), which calculates the level of dependence between the data [41]. Due to the hierarchical structure of the data, multilevel models will be used to simultaneously test for differences in the prevalence of outcomes between times and between groups, considering schools as a modeling level (Gllamm Stata 14). All analyses will be adjusted by sex, socioeconomic level and site. The analyses will be performed in Stata 15 (descriptive analyses and multilevel GLLAMM), and a significance level of 5% will be adopted.

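### The 82% power describes a single-time-point comparison of binge drinking, but the stated analysis tests across times and groups without adjusting for the student's own baseline use; its power may fall below 82%, depending on a correlation the protocol does not give

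*Protocol article*

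**What the plan says.** The Sample size calculation section of the Protocol article plans 35 schools per arm and 90 students per school, or 3150 students per arm. It states that a sample of this size "will reach a power of 82% in identifying a difference between groups of 2.5% for the outcome of binge drinking in the past month". The other inputs it names are a 10% starting prevalence, an ICC of 0.005 and 5% significance. It gives no within-student correlation, names no visit and mentions no baseline measurement.

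The design has a baseline and two follow-ups: "Information will be collected from the students at three time points: preintervention and 9 and 18 months postintervention". Under Data analysis of the randomized controlled trial, "multilevel models will be used to simultaneously test for differences in the prevalence of outcomes between times and between groups". On covariates: "All analyses will be adjusted by sex, socioeconomic level and site". The student's own T1 answer is not on that list, although T1 collects it and the secret code described under Instrument is meant to link it to later questionnaires.

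**The concern.** A power figure applies to one test. The one given belongs to a comparison of two arms at one follow-up. The analysis described puts several waves in one model and tests differences over time and between arms together. The usual reading is that baseline enters as an outcome wave and the effect is the group-by-time term, a difference in change between arms.

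That contrast carries the sampling error of the baseline wave as well as that of the follow-up. It gains over a follow-up-only comparison only if baseline and follow-up are correlated strongly enough. For a yes/no behaviour at about 10% prevalence this is uncertain. Binge drinking is the only outcome with a power calculation, and the trial is meant to inform a decision on national dissemination. If the correlation is low, a true 2.5-point reduction would be missed more often than the protocol implies. Baseline data that could sharpen the comparison would also go unused in the main model.

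**Working it through.** **Inputs from Sample size calculation.** 35 schools per arm, 90 students per school (35 × 90 = 3150), 10% vs 7.5%, ICC 0.005, 5% significance (taken as two-sided).

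**Assumptions, not in the document.** 10% in both arms at baseline; no losses; within-student correlation r from 0.1 to 0.4; correlation c of school effects over time of 1 or 0.8. Formulas are on the linear (risk) scale, as an approximation to the logistic model.

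**1. The stated figure.**
- Design effect = 1 + 89 × 0.005 = 1.445; effective n = 3150 / 1.445 = 2180 per arm.
- SE = √[(0.09 + 0.069375) × 1.445 / 3150] = 0.00855; 0.025 / 0.00855 = 2.92.
- Power = 83.2% (normal) or 82.2% (t, 68 df).
- The 82% is therefore reproduced as a comparison at one time point. With 10% vs 12.5% the power is 74.3%, which does not match.

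**2. Visit-specific group-by-time contrast, baseline means free.** With va and vb the Bernoulli variances at baseline and follow-up, the variance of one arm's mean change is

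[(va + vb − 2r√(va·vb)) × 0.995/90 + 0.005 × (va + vb − 2c√(va·vb))] / 35.

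Example, r = 0.2, c = 1:
- Control arm (0.09, 0.09): 0.18 × 0.8 × 0.995/90/35 = 4.55 × 10⁻⁵.
- Intervention arm (0.09, 0.069375): 4.06 × 10⁻⁵.
- SE = √(8.60 × 10⁻⁵) = 0.00928; ratio 2.70; power 76% (t, 68 df).

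| | r = 0.1 | 0.2 | 0.3 | 0.4 |
|---|---|---|---|---|
| c = 1 | 71% | 76% | 81% | 87% |
| c = 0.8 | 67% | 71% | 76% | 82% |

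The crossing point is r of about 0.3 when school effects are fully stable and about 0.4 when c = 0.8. A simulation of clustered binary data analysed on school means points the same way. At a within-student correlation of about 0.18 and school autocorrelation 0.5 to 1, the change contrast has 63% to 76% power and the single-time-point comparison about 82%. At about 0.57 the change contrast has 82% to 95%.

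**3. Both follow-ups pooled.** For the mean of T2 and T3 minus T1, the bracketed term becomes va + vb(1 + q)/2 − 2q√(va·vb), with q = r at student level and q = c at school level. Assuming the same 2.5-point effect at both visits and equal correlation between all waves, power at r = 0.1 to 0.4 is 82%, 86%, 90%, 94% (c = 1) or 78%, 82%, 86%, 90% (c = 0.8).

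**4. Use of baseline.** Let ρ be the correlation between baseline and follow-up arm-level estimates. Taking equal variances at both waves and relative to the single-time-point comparison, the change contrast multiplies the variance by 2(1 − ρ) and optimal baseline adjustment multiplies it by 1 − ρ². Since 2(1 − ρ) − (1 − ρ²) = (1 − ρ)² ≥ 0, adjustment is never less precise than the change contrast. Since 1 − ρ² ≤ 1, it is never less precise than ignoring baseline.

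A conservative calculation multiplies only the student-level variance by 1 − r² and leaves school variance untouched. It gives 82%, 83%, 85%, 86% at r = 0.1 to 0.4. The 86% at r = 0.4 lies just under the 87% of the change contrast with c = 1 only because that calculation credits nothing to stable school effects. In the simulation, which adjusts for baseline school means, the adjusted comparison was ahead in every setting, for example 84% to 89% against 63% to 76% at a within-student correlation of about 0.18.

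**The case against.** A reader might infer that the stated analysis simply has less power than 82%, or that the trial is underpowered for binge drinking. The documents do not support that, for these reasons, all of which stand:

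- **The deciding contrast is inferred.** The analysis section names no interaction term, coefficient or visit. Visit-specific arm contrasts, or a model with a common baseline, would also fit its wording. An article may leave that choice to an analysis plan that is not shown.
- **No correlation is given.** Weak tracking of past-month binge drinking is plausible but is an assumption. At r = 0.4 the visit-specific change contrast reaches 82% to 87%.
- **There are two follow-ups.** A contrast that pools them has about 78% to 94% power over the same range of r.

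A reader might also take school to be the only random level, which would give other power figures (about 74% to 78%). The text calls schools a modelling level and names both school and class as sources of dependence, so the point should not rest on that reading. Nor is baseline ignored throughout: incidence outcomes depend on prior use, and the latent transition analysis follows students from their earlier state.

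Sizing with a simple formula and analysing with a multilevel model is not in itself an error. What the objection leaves untouched is that the article fixes both a power figure and an analysis, that the figure does not describe that analysis on its likely reading, and that the covariate list omits an already collected baseline value that can only help precision.

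**Conclusion.** The point holds in conditional form. The 82% is the power of a two-proportion cluster comparison at one time point, not of a model testing across times and groups. If the deciding test is a visit-specific group-by-time contrast with free baseline means, power for binge drinking is below 82% when the within-student correlation is under about 0.3 (fully stable school effects) or 0.4 (school autocorrelation 0.8). At a correlation of 0.1 to 0.2 it is about 67% to 76%, a shortfall of roughly 6 to 15 points. Above those thresholds there is no shortfall, and pooling the follow-ups largely removes it.

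The efficiency point depends on neither the unknown correlation nor the reading of the test. Under randomisation, adjusting for baseline use or holding the arms to a common baseline is at least as precise as the matching unconstrained change contrast. All figures assume no losses and 10% prevalence in both arms at baseline.

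**What to change.** In Data analysis of the randomized controlled trial, define the treatment effect as the between-arm difference in prevalence at T2 and at T3, and do one of the following:

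- add the student's T1 value of the same outcome to sex, socioeconomic level and site; or
- keep T1 as a wave in the longitudinal model, with one common baseline mean for both arms. This also retains students whose T1 code cannot be matched.

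This is the comparison the sample size was calculated for, so 82% becomes approximately a lower bound before losses. The change concerns the past-month and past-year prevalence outcomes. For incidence among students with no use at T1 the baseline value is constant and adds nothing.

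If a group-by-time test is preferred, restate the power in Sample size calculation for that test, naming the visit or visits and the assumed within-student correlation with its range.

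The cost is wording only: no new data and no more schools. The one drawback is that the covariate version needs a rule for students with no matched T1 questionnaire, such as a missing-baseline indicator; the common-baseline version does not.

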### Randomization

Schools from each of the participating municipalities registered in the INEP’s national registry of schools will be randomly selected. The schools must meet the following inclusion criteria: (a) a public school and (b) have at least three 8th grade classes. Thirty schools will be drawn in Fortaleza, 30 schools in São Paulo and 10 schools in Eusébio. Among the schools selected to participate in the study, a second random draw will define which schools will be included in the control group and which will be included in the experimental group, maintaining a ratio of 1:1 in the number of control and experimental schools in each municipality. After selecting the schools, a list with the names of the selected schools will be forwarded to each education department of the participating municipalities to request authorization for participation in the study. Due to the involvement of the government, all schools typically agree to participate, as occurred in a previous study [16].

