Some limitations of this study must be noted. The main limitation is related to the known high rate of school absences of the Brazilian student population, which could result in bias. However, this is a common limitation to longitudinal studies [48–50], and the goal is to try to minimize it by giving prior notice to the students about the researchers’ visit for data collection, which did not occur in previous versions of the study [16]. Another limitation of the study is that the information is obtained through self-reporting by the students themselves. Although this method may lead to measurement bias, self-reporting is the most recommended evaluation method for adolescents and has been found to have excellent validity in studies evaluating drug-related behaviors [51, 52]. Currently, there are no viable alternatives for collecting data on alcohol use in adolescent samples, as biological measures would not be appropriate in a sample in the early stages of alcohol use [53]. To avoid the overreporting of drug use, a question of the use of fictitious drugs (holoten and carpinol) has been added to the questionnaire to screen this problem. In cases where the student responds positively to these drugs, the questionnaire will be excluded from the study, reducing the information bias [54].

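### The 6300 students are said to allow for losses to follow-up, but 6300 is the number that must be analysed for the stated 82% power, so no loss margin is shown

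*Protocol article*

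**What the plan says.** The sample size section of the protocol article sets the requirement as "A sample size of at least 3150 adolescents in the control group and 3150 in the intervention group". Each arm is spread over 35 schools, with a floor of 90 that I read as students per school, because 35 × 90 = 3150. The claim made for this size is that it "will reach a power of 82% in identifying a difference between groups of 2.5% for the outcome of binge drinking in the past month". Behind that figure stand a starting prevalence of 10%, a 5% significance level and an ICC of 0.005. The section then concludes that "70 schools will be selected to ensure a minimum sample size of 6300 adolescents, considering possible losses to follow-up".

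The study design section describes the trial as "totaling approximately 6300 students distributed in 210 groups". The abstract gives the same total and calls these students participants. Outcomes are measured at 9 and 18 months.

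Under strengths and limitations, the main limitation is the "known high rate of school absences of the Brazilian student population, which could result in bias". The same section says that a questionnaire endorsing a fictitious drug will be excluded. No loss rate is given anywhere in the article.

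**The concern.** A sample size that allows for losses has two numbers: how many must be analysed, and a larger number to be enrolled so that enough remain. Here both are 6300. The text claims an allowance that its own figures do not contain. This is not a detail left to a fuller document, because the article asserts the allowance.

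It matters because 82% is the only power figure given, and the trial is meant to inform a decision on national dissemination. A reader will take 82% as the power after ordinary attrition at 9 and 18 months, when on these figures it applies only if every planned student is analysed.

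**Working it through.** **Inputs from the article.** 35 schools per arm; 90 students per school; ICC 0.005; prevalence 10%; difference 2.5 percentage points; significance level 5%. Allocation is 1:1, "maintaining a ratio of 1:1 in the number of control and experimental schools in each municipality". The number of sides is not stated; I assume two. The direction is not stated in the sample size section; I take a fall to 7.5%, since the Aims section hypothesises a decrease.

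**Step 1: the two totals.**
- Number behind the power: 2 × 35 × 90 = 6300.
- Planned participation: about 6300 in 210 classes. 70 schools × 3 classes = 210, and 6300 / 210 = 30 students per class (derived; the article does not state a class size).
- Difference available for losses: 6300 − 6300 = 0.

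**Step 2: reproduce the 82%.**
- Design effect = 1 + (90 − 1) × 0.005 = 1.445.
- Effective n per arm = 3150 / 1.445 = 2180.
- Standard error = √[(0.10 × 0.90 + 0.075 × 0.925) / 2180] = √(0.159375 / 2180) = 0.00855.
- Difference / standard error = 0.025 / 0.00855 = 2.92.
- Normal approximation: Φ(2.92 − 1.96) = 83.2%.
- Noncentral t with 2 × (35 − 1) = 68 degrees of freedom: 82.2%.

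The t version matches the stated 82%, and it does so with all 3150 per arm analysed.

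**Step 3: direction.** For 10% against 12.5% with no losses, two-sided, the variance sum is 0.09 + 0.109375 = 0.199375. Power is then 73% (t) or 74% (normal). A one-sided test for a rise would also give about 83%, but the stated hypothesis is a decrease. So, two-sided, the 82% belongs to a reduction to 7.5%.

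**Step 4: power under assumed losses.** The loss rates below are assumptions, not figures from the article. All 35 schools per arm are kept and the number analysed per school becomes m = 90 × (1 − loss). Effective n = 35m / [1 + (m − 1) × 0.005].

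| Assumed loss | m | Analysed, both arms | Effective n per arm | Power, t (68 df) | Power, normal |
|---|---|---|---|---|---|
| 0% | 90 | 6300 | 2180 | 82% | 83% |
| 10% | 81 | 5670 | 2025 | 79% | 80% |
| 20% | 72 | 5040 | 1860 | 76% | 77% |
| 30% | 63 | 4410 | 1683 | 72% | 73% |
| 40% | 54 | 3780 | 1494 | 67% | 68% |

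Power passes below 80% at about 8% loss by the t version and about 11% by the normal approximation.

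**Step 5: what an allowance would have looked like.** To leave 6300 analysed, enrolment would be 6300 / (1 − loss): 7000 at 10%, 7875 at 20%, 9000 at 30%. No total of this kind appears in the article.

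**The case against.** The strongest reply is that the section words its quantities as floors: at least 3150 per arm, at least 90 students, at least three classes per school, a minimum of 6300. Schools with more than three classes are eligible, and the intervention section has all 8th grade students in experimental schools receiving the programme. Recruitment could exceed 6300, and 6300 could even be meant as what remains after losses. This stands in part: a reader might infer that the trial is bound to miss its stated power, and the documents do not support that. But the abstract and study design give about 6300 in 210 classes as participation, and no surplus is planned or quantified. What can be said is that no margin is shown.

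A second reply is that the effect is moderate, because losses shrink schools rather than remove them. That is right: about 3 points at 10% loss and 6 at 20%. It limits the size of the point but does not remove the contradiction.

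Three further inferences should be resisted:
- Failed matching of the students' secret codes should not be counted as full loss. The article does not say that unmatched questionnaires are discarded, and the planned multilevel model compares prevalence between times and groups.
- The earlier Brazilian trial's attrition cannot be used as the planning value from these documents, which do not report it. Students will also now receive prior notice of data collection, which they did not before.
- The lower power for an increase is not an error in the plan. The hypothesis is a reduction, and the harm reported earlier was on alcohol initiation, not on past-month binge drinking, the outcome used for sizing.

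**Conclusion.** The point holds. The sample size section claims an allowance for losses that its figures do not contain: 2 × 3150 = 6300 is both the number giving 82% power and the planned participation. The 82% should be read as the power with every planned student analysed, for a two-sided test of a fall from 10% to 7.5%.

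The size of any shortfall depends on a loss rate that the documents do not give. Across assumed losses of 10% to 40%, power runs from about 79% down to 67% by the t version, or 80% down to 68% by the normal approximation. These figures also assume equal school sizes, losses spread evenly over schools, and the stated ICC and prevalence. This is an error in a stated property of the design. It does not show that the design is inadequate or that the power achieved will fall short.

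**What to change.** In the sample size section:

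1. Delete the closing claim about losses to follow-up. Alternatively, if an allowance was made, show it: the assumed loss rate, the number to be analysed, and the larger number to be enrolled.
2. State that 82% assumes all 3150 students per arm are analysed, a two-sided 5% test (if that is what was used), and a reduction from 10% to 7.5%.
3. Give the power at the analysed number the sponsor expects at 9 months and at 18 months, with the source of each loss rate.
4. Use one method throughout. If 82% is kept as the starting figure, the accompanying values are the t-based ones (about 79%, 76%, 72% and 67% at 10%, 20%, 30% and 40% loss). The normal-approximation series starts from 83% and should not be mixed with it.

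The cost is one paragraph of wording and a less favourable stated power. No schools need be added and no procedure changes.
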